### Objective 2: Degree of agreement of SpHb and CBC

**
*Agreement of anemia status (binary measure)*
**

**Positive percentage agreement and negative percentage agreement**

Positive percentage agreement (PPA) and negative percentage agreement (NPA) measure the level of agreement between two sets of binary measures. Here, both PPA and NPA will be used to examine the level of agreement between test methods (SpHb/CBC) in identifying anemia in pregnant women (i.e. anemic/healthy). Bootstrap 95% confidence intervals will be obtained for PPA and NPA based on repeated measurements where observations from the same participant will be sampled or not sampled together.

PPA=#positive(anemia)bySpHb/#positive(anemia)byCBC

NPA=#negative(healthy)bySpHb/#negative(healthy)byCBC

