### Study sample

**
*Recruitment of participants*
**

A sample of 900 pregnant women from each site will be selected from the PRISMA study primary cohort, for a total of 2700 participants. Participants may be recruited sequentially through household-based or facility-based pregnancy surveillance (e.g., the first 900 women enrolled in PRISMA will also be included in this study from the date of protocol approval per site).

**
*Eligibility criteria*
**

Any participant that is eligible for the PRISMA study is also considered eligible for this study. However, research staff may exclude women from the study, based on the presence of injury, deformity, tattoo, or birthmark that interferes with Masimo sensor placement or performance or a finger size that does not appropriately fit the device. Presence of henna, nail polish or long nails is not an exclusion criterion, but staff will record information about these factors as they might interfere with the Masimo device performance.

**
*Consent*
**

PRISMA MNH uses a multiphase process to recruit women through pregnancy surveillance. Consent or assent will be obtained from pregnant women after a pre-screening process to determine eligibility in the PRISMA MNH study.

**
*Study status*
**

The parent PRISMA MNH study began recruiting and enrolling pregnant women on 22 September 2022 (Pakistan), 23 November 2022 (Kenya), and 15 December 2022 (Zambia). The study is planned to complete enrollment at the end of 2025. 

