**McNemar test**

McNemar test is a non-parametric test used to examine the change in proportion for repeated measures of matched paired data
^
16
^.

The test statistic is defined such that k=1,...,K represents different time points and within the kth cluster, b
_k_ and c
_k_ are the number of disagreeing pairs (b
_k _: anemia according to SpHb while normal according to CBC; c
_k _: normal according to SpHb while anemia according to CBC). Under the null hypothesis of no difference in the two systems (SpHb, CBC) of anemia classifications,
*χ*
^2^ is asymptotically distributed as a chi-square with one degree of freedom for a large number of clusters
*K*→∞

$$\chi 2=\frac{K-1}{K}\frac{{\left[\sum_{k=1}^{K}\;(b_{k}-c_{k})\right]}^{2}}{\sum_{k=1}^{K}\;{\left(b_{k}-c_{k}\right)}^{2}}$$

**
*Agreement of anemia severity (ordinal measure)*
**

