### Sample size considerations

**
*Total sample size*
**

The total sample size of 900 per study site will give 90% power for site-specific analyses to detect a systematic shift (defined as mean difference between each pair of SpHb and CBC divided by the standard deviation of all paired differences) of size 0.108 between the mean of SpHb measurements and the mean of CBC measurements. That is, if the SpHb system shifts from the reference CBC measurements by 10.8% of the SD of the mean difference, the probability that we will detect such a systematic shift using one sample t-test with significance level 0.05 is 90%. The total sample size of 900 will also give 80% power to detect a systematic shift of size 0.093*SD between the mean of SpHb measurements and the mean of CBC measurements. The SD can be calculated in the same way as those in the Bland Altman plots. However, 900 is a very conservative estimate of the sample size and would be sufficient to analyze the three sites independently. Based on our pilot data from Kenya and Pakistan, the mean difference between SpHb and CBC is approximately 0.8 times its SD; even a sample size as small as 19 pairs would provide 90% power using one-sample t-test.

In detecting the extreme differences (i.e. large absolute value) between the SpHb and CBC measures on the same sample, the sample size of 900 will give 99.99% probability to detect the top 1% largest values in the distribution of all differences. It will also give 98.90% probability to detect the top 0.5% largest values in the distribution of all differences, and 93.31%, 83.50%, 59.36% probability to detect the top 0.3%, 0.2%, 0.1% largest values in the distribution of all differences, respectively. With three repeated measures from each of the 900 participants, the listed probabilities are conservative estimates of chances in catching extreme values.

**
*Strata sample size*
**

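### PPA and NPA are printed as ratios of marginal counts, so they do not measure agreement: they equal 100% when errors cancel, and otherwise one of them exceeds 100%

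*Protocol article*

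**What the plan says.** Under Objective 2, in the section on positive and negative percentage agreement, the protocol article says that these statistics "measure the level of agreement between two sets of binary measures" and applies them to SpHb and CBC as ways of identifying anemia in pregnant women. It then prints two definitions:

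- "PPA=#positive(anemia)bySpHb/#positive(anemia)byCBC"
- "NPA=#negative(healthy)bySpHb/#negative(healthy)byCBC"

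On uncertainty it adds: "Bootstrap 95% confidence intervals will be obtained for PPA and NPA based on repeated measurements", with all of a participant's observations resampled together. No other section redefines either measure.

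The neighbouring sections do work with pairs. The Cohen's kappa section counts samples that both methods place in the same category. The McNemar section names the two discordant cells: "anemia according to SpHb while normal according to CBC" and "normal according to SpHb while anemia according to CBC".

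**The concern.** With CBC as the reference, PPA should be the share of CBC-anemic measurements that SpHb also calls anemic, and NPA the share of CBC-healthy measurements that SpHb also calls healthy. The printed numerators carry no such restriction. The PPA numerator includes SpHb's false positives, and the NPA numerator includes the anemic cases that SpHb missed.

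PPA and NPA are the first statistics the abstract lists for the binary objective, and its conclusion frames the study around diagnosing anemia. They are also the only planned measures that report missed anemia and false alarms separately as rates against CBC. Computed as printed, a device that misclassifies many women but reproduces the overall prevalence would be reported as agreeing perfectly.

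**Working it through.** **Inputs.** The two printed formulas, the discordant cells from the McNemar section, and a table size of 900 pairs ("A sample of 900 pregnant women from each site will be selected from the PRISMA study primary cohort", one pair per woman). Write the paired table as:

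- a = anemic by both
- b = anemic by SpHb only
- c = anemic by CBC only
- d = healthy by both

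The plan gives no PPA or NPA value to reproduce.

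**Formulas.**

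| | Printed | Concordant pairs | Printed minus concordant |
|---|---|---|---|
| PPA | (a+b)/(a+c) | a/(a+c) | b/(a+c) |
| NPA | (c+d)/(b+d) | d/(b+d) | c/(b+d) |

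The last column is never negative, so the printed values can only flatter the device.

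Subtracting 1 from the printed forms gives PPA − 1 = (b − c)/(a+c) and NPA − 1 = (c − b)/(b+d). Two results follow:

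1. If b = c, both are exactly 100%, whatever a and d are.
2. If b ≠ c, the two differences have opposite signs, so exactly one measure exceeds 100%. Enumerating all 5,394 two-by-two tables with n = 30 and non-zero denominators found no exception to either result.

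**Worked tables, n = 900 (illustrative counts).**

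| a / b / c / d | Printed PPA | Printed NPA | Concordant PPA | Concordant NPA | Pairs discordant | Kappa |
|---|---|---|---|---|---|---|
| 150/150/150/450 | 300/300 = 100% | 600/600 = 100% | 150/300 = 50.0% | 450/600 = 75.0% | 33.3% | 0.25 |
| 0/300/300/300 | 300/300 = 100% | 600/600 = 100% | 0/300 = 0% | 300/600 = 50.0% | 66.7% | −0.50 |
| 250/150/50/450 | 400/300 = 133.3% | 500/600 = 83.3% | 250/300 = 83.3% | 450/600 = 75.0% | 22.2% | 0.54 |
| 200/40/100/560 | 240/300 = 80.0% | 660/600 = 110.0% | 200/300 = 66.7% | 560/600 = 93.3% | 15.6% | 0.63 |

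The second row is the extreme case: no woman is called anemic by both methods, yet both printed measures are 100%.

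**Illustration at the pilot shift.** The sample size section reports that "the mean difference between SpHb and CBC is approximately 0.8 times its SD", without giving the direction. The remaining inputs are assumptions, not protocol figures: CBC hemoglobin normal with mean 11.0 to 11.5 g/dL and SD 1.3, SD of differences 0.8 to 1.2 g/dL, and one anemia cut-off of 11 g/dL. Simulation over that range gives:

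| Shift | Printed PPA | Concordant PPA | Printed NPA | Concordant NPA |
|---|---|---|---|---|
| SpHb low by 0.8 SD | 133–172% | 91–95% | 59–71% | 51–68% |
| SpHb high by 0.8 SD | 59–68% | 47–62% | 119–141% | 92–96% |

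With no shift and a CBC mean of 11.0, the printed values are 100% and 100%, while the concordant values run from about 76% to 82%.

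**The case against.** The strongest reply has four parts.

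- **Shorthand.** The one-line formulas may abbreviate SpHb-positive among CBC-positive, since the authors handle pairs correctly for kappa and McNemar. That is possible, but nothing in the text supplies the condition, and NPA repeats the same form. An analyst who codes what is printed gets the wrong quantity.
- **Secondary role.** The abstract makes the intraclass correlation and Bland–Altman analyses the primary objective, and the sample size rests on paired differences. This is true. The error does not touch the primary analysis, the power figures, kappa, McNemar or Objective 3.
- **It would be noticed.** Kappa on the same pairs would expose poor agreement (0.25 and −0.50 in the first two tables), and a value above 100% would alert anyone. This stands in part: an undetected error needs b close to c. But kappa does not separate missed anemia from false alarms, and McNemar asks the same marginal question as the printed ratios, so it too is blind when b = c. Moreover, when one measure is visibly impossible, the other still looks plausible and is also inflated.
- **The cancelling example is unlikely.** A pilot shift of 0.8 SD makes exact cancellation improbable unless the shift has little effect at the anemia cut-off. This is fair, but the alternative is then a value above 100%. The simulated figures depend on assumed inputs; the algebra does not.

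**Conclusion.** The point holds. As printed, PPA and NPA compare how many women each method labels anemic or healthy, not whether the methods agree on the same measurement, which contradicts their stated purpose. The result is either 100% for both, when errors cancel, or one value above 100%. On one data set the two cannot both exceed 100%. Each printed measure overstates its correct value, by b/(a+c) for PPA and c/(b+d) for NPA. In the first worked table that is 50 and 25 percentage points. These results follow from the formulas alone. Only the figures at the pilot shift depend on the assumed hemoglobin distribution and cut-off. The bootstrap does not help, because it would put intervals around the wrong estimand. This should be corrected before analysis.

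**What to change.** Replace the two definitions with:

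- PPA = number of pairs anemic by both SpHb and CBC, divided by number anemic by CBC, i.e. a/(a+c)
- NPA = number of pairs healthy by both SpHb and CBC, divided by number healthy by CBC, i.e. d/(b+d)

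Both then lie between 0% and 100%. Keep the participant-level bootstrap as planned and apply it to these quantities. If the printed lines were meant as shorthand for this, the change only makes the intention explicit.

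The cost is two formulas and the matching lines of analysis code. Data collection and sample size do not change. The reported values will be lower than the printed formulas would give wherever there are false positives (PPA) or missed cases (NPA).

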**Cohen’s kappa**

Cohen’s kappa is a measure of interrater reliability, where 0 indicates agreement equivalent to chance and 1 indicates perfect agreement. For repeated measures of matched pair data, the variance of kappa can be estimated nonparametrically
^
15
^. In this study it will be used to assess the agreement between two procedures (CBC and SpHb) in the independent matched-pair data using defined strata. For example, if both the CBC and SpHb classify a sample as “severe deficiency”, the samples will be rated as “in agreement”. Total number of samples in agreement will be counted and Cohen’s kappa will be calculated as follows:

$$\text{k}=({\text{P}}_{\text{o}}-{\text{P}}_{\text{e}})\text{/}({\text{1-P}}_{\text{e}})$$

Where, P
_o_ is the
*observed* level of agreement and P
_e_ is the
*expected* level of agreement. Here, the observed level of agreement is the proportion of the cases the two techniques agree upon. The expected level of agreement is the proportion of agreement that is expected by change.

**McNemar test**

McNemar test is a non-parametric test used to examine the change in proportion for repeated measures of matched paired data
^
16
^.

The test statistic is defined such that k=1,...,K represents different time points and within the kth cluster, b
_k_ and c
_k_ are the number of disagreeing pairs (b
_k _: anemia according to SpHb while normal according to CBC; c
_k _: normal according to SpHb while anemia according to CBC). Under the null hypothesis of no difference in the two systems (SpHb, CBC) of anemia classifications,
*χ*
^2^ is asymptotically distributed as a chi-square with one degree of freedom for a large number of clusters
*K*→∞

$$\chi 2=\frac{K-1}{K}\frac{{\left[\sum_{k=1}^{K}\;(b_{k}-c_{k})\right]}^{2}}{\sum_{k=1}^{K}\;{\left(b_{k}-c_{k}\right)}^{2}}$$

**
*Agreement of anemia severity (ordinal measure)*
**

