## Methods

### Study design

This proposed study will use a prospective cohort design nested within the ongoing PRISMA MNH open cohort study (see
Figure 1). Three sites currently using Masimo devices will participate: Lusaka, Zambia; Kisumu and Siaya, Kenya; Karachi, Pakistan. Each site has identified defined geographic regions that are appropriate for longitudinal data collection and the conduct of ongoing research involving pregnant women. Hemoglobin measurements for the validation study will occur at five timepoints: <20 weeks, 20 weeks, 28 weeks, 36 weeks’ gestation, and six weeks postpartum. The study sites in Pakistan will also collect measurements at week 32.

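### The clustered McNemar test takes visits rather than women as clusters; with five visits its statistic is capped at 4.0, its chi-square reference does not apply, and it loses power for small or uneven bias

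*Protocol article*

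**What the plan says.** Under Objective 2, the McNemar test section of the protocol article compares anaemia classification by the two methods over repeated visits. It defines the index as follows: "The test statistic is defined such that k=1,...,K represents different time points". The same sentence calls each time point a cluster, within which b_k and c_k count the two kinds of disagreeing pairs. The statistic is ((K−1)/K)·[Σ(b_k−c_k)]² / Σ(b_k−c_k)². The article states that it "is asymptotically distributed as a chi-square with one degree of freedom for a large number of clusters", with K tending to infinity.

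The number of visits is in the Study design section: "Hemoglobin measurements for the validation study will occur at five timepoints". It adds: "The study sites in Pakistan will also collect measurements at week 32". So K is 5 in Kenya and Zambia and 6 in Pakistan.

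Two other parts of Objective 2 treat the woman as the unit. The bootstrap intervals for positive and negative percentage agreement, and those for weighted kappa and the concordance index, keep or drop all of a participant's observations together.

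**The concern.** The statistic is a cluster-level test. It takes one net discordance per cluster, d_k = b_k−c_k, and judges the sum of these against their own spread. The chi-square reference needs many clusters that are independent of one another. Women meet that condition and visits do not: there are only five or six of them, and the same women contribute to each.

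An analyst who follows the text would compute a test whose null distribution is not the stated one. With five terms, the statistic mostly reflects how even the net discordance is from visit to visit, rather than whether it differs from zero. A real tendency of the device to over- or under-call anaemia could then give a non-significant result because its size varies over gestation or because attendance varies between visits.

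**Working it through.** The article states no size or power for this test, so there is no figure of its own to reproduce. No significance level is stated for it either. Two-sided 0.05 is assumed, as in the sample size section, giving a critical value of 3.841.

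**Inputs from the article.** K = 5, or 6 in Pakistan (Study design); 900 women per site (Study sample: "A sample of 900 pregnant women from each site will be selected"); the formula above.

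**Ceiling (no assumptions).** By Cauchy–Schwarz, (Σd_k)² ≤ K·Σd_k², so the statistic is at most ((K−1)/K)·K = K−1.

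**Condition for rejection.** Let CV be the coefficient of variation of the d_k (SD with divisor K). Then the statistic equals (K−1)/(1+CV²). Rejection needs CV² < (K−1)/3.841 − 1.
- K=5: CV² < 4/3.841 − 1 = 0.0413, so CV < 0.203.
- K=6: CV² < 5/3.841 − 1 = 0.302, so CV < 0.549.

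**Null size if the d_k are independent, normal and of equal variance.** The statistic equals (K−1)t²/(K−1+t²), where t is the one-sample t of the d_k on K−1 df. Setting it to 3.841 gives |t| > 9.84 for K=5 and |t| > 4.07 for K=6.

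| K | Maximum | Smallest p | Null size |
|---|---|---|---|
| 5 | 4.0 | 0.0455 | 0.06% |
| 6 | 5.0 | 0.0253 | 0.96% |
| 900 (women) | 899 | effectively 0 | 4.98% |

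**Null size if visit totals are correlated.** At K=5, equicorrelated normal d_k give 0.5%, 1.6%, 5.0% and 22% at correlations of 0.3, 0.5, 0.7 and 0.9. In simulations of 900 women with 10% discordance each way and a latent within-woman correlation of 0, 0.3 or 0.5, size was 0.1%, 0.2% and 0.5% at K=5. At K=6 it was 1.2%, 4.3% and 9.3%, so in Pakistan the error can go either way. With women as clusters it was 4–6% throughout.

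**Worked patterns at K=5, all biased in one direction.**
- d = 120, 100, 110, 90, 80: sum 500, sum of squares 51,000; 0.8 × 250,000/51,000 = 3.92, rejected.
- d = 150, 100, 120, 80, 50: sum 500, sum of squares 55,800; 0.8 × 250,000/55,800 = 3.58, not rejected.
- Constant 20% net discordance with attendance of 900, 450, 800, 750 and 700: d = 180, 90, 160, 150, 140, sum 720, sum of squares 108,200; 0.8 × 518,400/108,200 = 3.83, not rejected. Uneven attendance alone is enough.

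**Power at K=5, 900 women.** Discordance rates and correlations (0 to 0.5) are assumptions; the article gives none.

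| Discordance, b vs c | Visits as clusters | Women as clusters |
|---|---|---|
| 12% vs 10% | 2–6% | 50–82% |
| 15% vs 10% | 27–42% | 99–100% |
| 20% vs 10% | 79–95% | 100% |
| 25% vs 5% | 100% | 100% |

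On the haemoglobin scale (assumed Hb SD 1.3 g/dL, difference SD 1.0 g/dL, cut-off 11.0 g/dL, within-woman correlation 0.3–0.5), a 0.2 g/dL shift was rejected about 26–53% of the time as written and 100% with women as clusters. At 0.8 g/dL the test as written rejected 97–100%. With assumed visit means of 11.8, 11.3, 10.9, 11.2 and 12.2 and a shift of +0.8, it rejected 0% against 100% with women as clusters; at −0.8 both rejected 100%.

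**The case against.** The strongest reply is that the index is merely mislabelled. The formula and the large-K condition both fit women as clusters, and the bootstraps under the same objective already resample by participant. That is a plausible account of what was meant, but the text names time points and calls each one a cluster, so it needs correcting either way.

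The second reply is about consequence, and it stands. McNemar belongs to the second objective and sits beside percentage agreement and kappa. The primary objective rests on the intraclass correlation and Bland–Altman analysis, and the sample size on a one-sample t-test. The article does not say how a non-significant McNemar result would be interpreted.

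A reader might go further in three ways that the document does not support.
- **That the test almost never rejects.** This is true of the null at K=5 with independent or moderately correlated visit totals, not in general. The article reports a pilot mean difference of about 0.8 SD; a bias of that size, if even across visits, would be detected. The 0.06% figure itself assumes independence that these visits lack.
- **That an antenatal-only test could never reject.** With K=4 the ceiling would be 3.0, but no such test is planned, and Pakistan would have five antenatal visits.
- **That K might be 3.** The sample size section says "With three repeated measures from each of the 900 participants", which would cap the statistic at 2.0. That sentence concerns the chance of catching extreme differences, not this test, and Study design gives five visits.

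**Conclusion.** The McNemar test is wrong as written. The ceiling of K−1 and the failure of the large-K condition follow from the article alone. At K=5 rejection requires nearly equal net discordance at all visits. Null size is then far below 5% unless visit totals are very highly correlated (about 0.7 or more in the normal model). At K=6 it may fall below or above 5%. The power figures rest on assumed discordance rates, haemoglobin distribution, cut-off and within-woman correlation, and they move with the visit means. They support a conditional statement: much power is lost for small or uneven bias, while a large and even bias is still found. The test is secondary and no stated decision rule or sample size depends on it, so this is a point that should be fixed rather than one that threatens the main conclusions.

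**What to change.** Redefine k as the participant, so that K is about 900 per site (2,700 pooled), with b_k and c_k the numbers of that woman's visits discordant in each direction. Keep the formula and the chi-square(1) reference. This matches the participant-level resampling already specified under Objective 2. Where a result for a single visit is wanted, use the ordinary paired McNemar test at that visit. Visits should not simply be pooled in an unclustered McNemar test: in the five-visit null simulations its size was 15–19% at latent within-woman correlations of 0.3–0.5. The cost is one sentence of wording, with no new data.

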**Weighted Cohen’s kappa**

Weighted Cohen’s kappa is a measure of interrater reliability for ordinal or categorical items, in this case, for anemia severity (mild, moderate, severe, healthy, above normal). Linear or quadratic weights are assigned to different combinations of SpHb category (i) + CBC category (j). The equation for weighted κ is below, where i, j represents the category judging from SpHb and CBC respectively. Furthermore, w
_ij_, O
_ij_ and e
_ij_ are elements in the weight, observed counts, and expected counts matrices, respectively. 

$$\kappa =1-\frac{\sum \;}{}\frac{\sum_{i=1}^{4}\;\;\sum_{j=1}^{4}\;w_{ij}o_{ij}}{\sum_{i=1}^{4}\;\;\sum_{j=1}^{4}\;w_{ij}e_{ij}}$$

